**Baseline Data:**

- Baseline annualized rate of the primary outcome in the resident's facility (last 3 years)
- Age
- Gender
- Location (Calgary / Edmonton / Other)
- Level of Care Designation (Long Term Care, Long Term Care-Dementia, Supportive Living, Supportive Living-Dementia, Personal Supportive Living)
- Length of stay in LTC facility
  - New admission (last 60 days)
  - Old Admission ( $\geq 3$  years)
- Charlson score

- Key Comorbidities - requiring 2 claims or 1 in-hospital diagnosis (any Dx, not just primary Dx) over the duration of available administrative claims:
  - Diabetes
  - Coronary Artery Disease (CAD)
  - Stroke
  - Osteoarthritis (OA)
  - Congestive Heart Failure (CHF)
  - Chronic Obstructive Pulmonary Disease (COPD)
  - Hip Fracture – for this characteristic only 1 diagnosis is required
  - Chronic Kidney Disease (CKD) – for this characteristic only 1 diagnosis is required (since family physicians rarely have CKD dedicated visits), or 2 GFR < 40
  - Dementia
  - $\geq 2$  of the above Key comorbidities
- TIA (1 claim or 1 in-hospital Dx)
- Stroke or TIA (1 claim or 1 in-hospital Dx)
- Dialysis (1 procedure)
- Total number of medications
- Total number of BP medications
- Days in hospital in prior 6 months
- Number of ER visits in prior 6 months
- *Collected for the purpose of inclusion / exclusion*
  - *Hypertension (2 claims or 1 in-hospital) – inclusion criteria*
  - *Any once daily hypertension medication – inclusion criteria*
  - *Glaucoma – exclusion*

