#### **D) Power/Sample Size Estimate:**

Expected Recruitment: At the time of this application we are collaborating with multiple ICCER-affiliated LTC organizations that wish to participate in this initiative. Most of these organizations have multiple facilities, many of which have multiple buildings or wings. Using Canadian Primary Care Sentinel Surveillance (CPCSSN) EMR data (accessed for the purpose of this application) we know that 53% of Canadians 80 yrs and older are listed as currently taking daily BP lowering medication. In our experience most of these medications are maintained upon nursing home admission. This suggests, given the 18-month median lifespan of newly admitted patients (and 9 month median lifespan of those already resident at the time of the study), that we should easily obtain 1200 residents total over the roughly 2-3-year duration of the trial.

Power: Utilizing well described methods for sample size determination, inflating the number of events to account for noncompliance, conservatively setting the median lifespan at 3 years to account for the inclusion of supportive living residents who, on average, live longer than the expected 18 months in long-term care facilities and assuming 33% of patients will be censored prior to any events, we find that 1232 patients would have 80% power (at a p of 0.05) to detect a difference between groups in the primary outcome of 27.6%. Although smaller differences would still be clinically meaningful, this difference is less than the 55% relative reduction in total mortality claimed in the MAPEC trial that we are trying to reproduce, and it is a very conservative minimum estimate for the actual power that the study will have. Additional power, while not directly calculable, will come in 2 ways: 1) These calculations assume no meaningful covariates and we have several covariates that are likely to be predictive of each outcome – in particular the resident's

level of care designation, and 2) we will continue to seek new facilities to partner with over the course of the trial – which should increase the number of residents available.

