### Selecting regression covariates

Analyses of dichotomous outcomes will use a maximum of 1 covariate per 10 outcomes, and analyses of continuous outcomes will use a maximum of 1 covariate per 20 randomized subjects. The covariate list for each analysis is predefined in table 2, and all are measured at baseline. We will always use the maximum number of covariates possible, selected in the order given (i.e. we will not undertake stepwise addition or subtraction). As we go down the covariate list, if one covariate has too many levels to be accommodated by the remaining number of outcomes or participants (e.g. facility, or level of care) we will skip it and go to the next covariate in the list.

| Table 2 Analysis Plan        |                          |                                                                                                  |
|-------------------------------------|--------------------------|--------------------------------------------------------------------------------------------------|
| Outcome                      | Method            | Baseline Covariates                                                                       |
| Primary                      |                          |                                                                                                  |
| Major adverse cardiovascular events | Cox Proportional Hazards | Age <70, Gender, Facility/Level of Care specific mortality rate (prior 3 years), New admission*, |

|                                                                                     |                          |                                                                                                                                                                                                                                                                                                                                |
|-------------------------------------------------------------------------------------|--------------------------|--------------------------------------------------------------------------------------------------------------------------------------------------------------------------------------------------------------------------------------------------------------------------------------------------------------------------------|

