|                                                                                     |                          | Old admission † , Days hospitalized in prior 6 months, Number of ED visits in prior 6 months, Charlson score, Facility, Total number of non-BP medications, Total number of BP medications, CHF, COPD, CKD, stroke, diabetes, CAD, sleep apnea                                                                      |
| Secondary Efficacy                                                           |                          |                                                                                                                                                                                                                                                                                                                                |
| All-cause mortality                                                                 | Cox Proportional Hazards | Same as for primary outcome                                                                                                                                                                                                                                                                                                    |
| Hospitalization for stroke
Hospitalization for MI/ACS
Hospitalization for CHF | Cox Proportional Hazards | Facility/Level of Care specific hospitalization rate (prior 3 years)                                                                                                                                                                                                                                                           |
| All-cause unplanned hospitalization / ED visit                                      | Cox Proportional Hazards | Facility/Level of Care specific hospitalization rate (prior 3 years), New admission*, Old admission) † , Days hospitalized in prior 6 months, Number of ED visits in prior 6 months, Charlson score, Age < 70, Gender, Total number of non-BP medications, Total number of BP medications, CHF, COPD, CKD, Diabetes |

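### The one-item covariate list for stroke, MI/ACS and CHF hospitalization can never admit the resident's own cardiovascular history, even if events allow it (optional, minor improvement)

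*Combined protocol and SAP*

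**What the plan says.** The rule is in the SAP under Selecting regression covariates. The cap is "Analyses of dichotomous outcomes will use a maximum of 1 covariate per 10 outcomes". Covariates come from a list fixed for each outcome in Table 2: "We will always use the maximum number of covariates possible, selected in the order given". A multi-level covariate that does not fit is passed over: "we will skip it and go to the next covariate in the list".

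In Table 2, the Secondary Efficacy row "Hospitalization for stroke Hospitalization for MI/ACS Hospitalization for CHF" is analysed by Cox regression with one listed covariate, "Facility/Level of Care specific hospitalization rate (prior 3 years". This is an aggregate rate specific to facility and level of care. It is not specific to stroke, MI/ACS or CHF, and no resident-level variable follows it.

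The protocol's Baseline Data section collects prior CHF, CAD and stroke. All three are on Table 2's primary-outcome list, which ends "Total number of BP medications, CHF, COPD, CKD, stroke, diabetes, CAD, sleep apnea"; all-cause mortality uses the same list.

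The protocol's Power/Sample Size section cites covariates as a source of extra power: "we have several covariates that are likely to be predictive of each outcome". It singles out level of care, which the aggregate rate partly carries. That sentence is background; the issue lies in the SAP's selection rule and Table 2.

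**The concern.** The row stands apart from the rest of Table 2. It is the only one with a single covariate and the only one with no resident-level variable. Neighbouring rows do what one would expect here:

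- Non-vertebral fracture pairs an aggregate fracture rate with the resident's own prior fracture.
- Urinary incontinence and skin ulceration list prior stroke, yet the stroke hospitalization model does not.
- All-cause unplanned hospitalization lists 14 covariates, including CHF, yet the CHF hospitalization model does not list it.

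The documents give no reason. Sparse events do not supply one, because the 1-per-10 cap already protects against overfitting by truncating a longer list. With one item listed, the instruction to use as many covariates as possible has nothing to act on beyond the first.

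The composite includes all-cause death, so these three models give the plan's only cardiovascular-specific efficacy results. Omitting a strong baseline predictor costs some precision, draws the hazard ratio slightly toward 1, and leaves the observed estimate more exposed to chance imbalance in that predictor.

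**Working it through.** **1. The plan's own figure.** Inputs from the protocol's power section: 27.6% reduction (taken as HR 0.724), 80% power, p of 0.05 (taken as two-sided), 1:1 allocation. Schoenfeld events = 4(1.960 + 0.842)² / (ln 0.724)² = 301.0. The stated 301 primary events reproduces. No corresponding count or rate is given for stroke, MI/ACS or CHF.

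**2. What the cap allows.** Budget = floor(component events / 10).

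| Component events | Budget | Current list uses | Rate + matching history fits? | Rate + all three histories fit? |
|---|---|---|---|---|
| under 10 | 0 | 0 | no | no |
| 10–19 | 1 | 1 | no | no |
| 20–29 | 2 | 1 | yes | no |
| 30–39 | 3 | 1 | yes | no |
| 40–49 | 4 | 1 | yes | yes |
| 100 | 10 | 1 | yes | yes |

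The SAP does not say whether the treatment term counts toward the cap. If it does, the thresholds of 20 and 40 become 30 and 50. Counting first events only, all three components reach 20 if together they supply 60 of the 301 (20%), and reach 40 with 120 of 301 (40%), evenly split.

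**3. How firmly the histories sit in the primary model.** At 301 events the budget is 30. Eight covariates precede Facility, leaving 22. With k facilities (k − 1 terms; k not stated), CHF, stroke and CAD all enter if k ≤ 15, or if k ≥ 24, when Facility is skipped. CAD drops out at k = 16–17, stroke and CAD at 18–20, and all three at 21–23. So they are on the primary list, but entry is conditional.

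**4. Power, by simulation.** All component inputs are assumed: 30% with prior history, treatment HR 0.6.

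- *Set A*: 1,232 residents, 3-year median lifespan, 1.5 years of follow-up, history HR 3 or 5, 400 runs each; unadjusted versus history-adjusted.
- *Set B*: 1,200 residents, death rate 0.3/yr, facility log-rate SD 0.3, history HR 5, 8 and 5 in the three rows below, stopped at 301 composite events, 1,500 runs each; aggregate rate alone versus rate plus history.

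| Set | Mean component events | Without history | With history |
|---|---|---|---|
| A | 16 | 11.8% | 11.3% |
| A | 22 | 19.5% | 18.8% |
| A | 39 | 36.5% | 36.0% |
| A | 52 | 43.3% | 45.3% |
| A | 76 | 56.3% | 58.0% |
| A | 100 | 70.3% | 71.5% |
| B | 45 | 35% | 36% |
| B | 59 | 44% | 48% |
| B | 76 | 54% | 59% |

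Below about 40 events there is no gain. Above that it is 1 to 5 points, largest when history is a strong predictor and events are many.

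**5. Chance imbalance.** Randomization uses blocks of 2 or 4 with no stratification. For a history with 30% prevalence in 1,200 residents, the SD of the between-arm difference is √(0.3 × 0.7 × 4 / 1200) = 0.026. A difference of 5 points or more is 0.05/0.0265 = 1.89 SD, about 6% of trials. For history hazard ratio h, the log HR moves by about (h − 1)/(1 + 0.3(h − 1)) per unit of imbalance: 1.25, 1.82 and 2.26 for h = 3, 5 and 8. A 5-point imbalance therefore moves it by 0.06, 0.09 or 0.11, a 6% to 12% change in HR. For scale, the standard error of the log HR is about 2/√D: 0.32 at 40 events and 0.23 at 76. The shift is less than half a standard error.

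**The case against.** The strongest reply is that this is a valid, prespecified, parsimonious model for three secondary outcomes. Treatment is randomized, so leaving out history does not invalidate the comparison, and chance imbalance is sampling error already covered by the confidence interval. That stands. A reader might infer that the unadjusted-for-history estimates are biased by imbalance; the documents do not support that.

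Nor does the SAP contradict itself. The maximum applies within a list fixed in Table 2, so a short list does not breach the rule. The protocol's mention of multiple patient-level covariates in its Statistical Analysis section concerns the primary outcome only.

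A reader might also infer that the histories fit the cap and that several permitted covariates are going unused. That cannot be shown, because no component counts are given. Death is in the composite. At a 3-year median lifespan (ln 2/3 = 0.231 per year), deaths alone would reach 301 in 301/0.231 ≈ 1,300 person-years, about 1.1 years for each of 1,200 residents. Counts of 10–19 for a component cannot be excluded, and one covariate is then exactly the maximum.

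Larger power gains, up to about 7 points, appear if follow-up is simulated over a full three years. That setup produces 460 to 501 composite events, well past the 301 at which the trial stops, so those gains should not be relied on.

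The reply does not explain why the list stops at one when the cap would already shorten a longer list, or why this row lacks the resident's own prior event when the fracture row has it.

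**Conclusion.** The point holds as an optional, minor improvement. As written, Table 2 prevents the selection rule from ever admitting the resident's own CHF, CAD or stroke history into the three component models, even at 20 or more events. The variables are already extracted for the primary list.

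The benefit is small: about 0 to 5 points of power, near zero below about 40 events, plus less sensitivity to chance imbalance. These sizes rest on an assumed 30% prevalence, history hazard ratios of 3 to 8 and a treatment HR of 0.6, none of which the documents supply. How many covariates would enter each model is unknown. The existing analysis remains valid, and nothing here bears on the primary outcome.

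**What to change.** In the Table 2 row for the three component hospitalizations, add the matching history next to the existing rate: CHF for CHF, CAD for MI/ACS, stroke for stroke. Follow these with the primary outcome's patient-level covariates in their present order, and let the 1-per-10 cap truncate the list. State whether the treatment term counts toward the cap.

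The cost is one table row and no new data. There is one trade-off to settle explicitly. If history is listed first and a component has only 10–19 events, it takes the single slot and displaces the facility/level-of-care rate. If the rate stays first, history enters only from 20 events.

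The amendment log's October 2024 entry already reports results. If analysis is complete, keep the planned models as they are and report the history-adjusted estimates as a labelled sensitivity analysis.

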## PLAN FOR DATA ANALYSIS:

**Interim Analysis:** An independent data safety monitoring board (DSMB) organized and chaired by [name] (Cochrane Hypertension Review Group Coordinating Editor) will review all data upon reaching 150 events (~18 months in). If  $p \leq 0.001$  for benefit (the

Haybittle-Peto boundary – recommended to reduce the chance of stopping too early and magnifying benefit), or if  $p \leq 0.05$  for harm, the DSMB will apply clinical judgement and make recommendations to the steering committee on whether the trial should break early.

**Statistical Analysis:** The primary outcome will be analyzed by a Proportional Hazards Survival Analysis using multiple patient level covariates including: Age <70, Gender, Location (Edmonton / Calgary / Other), New admission (< 60 days on date of randomization), Old admission ( $\geq 3$  years on date of randomization), Level of Care Designation (i.e. LTC, LTC-D, SL-D, SL, PSL), Days hospitalized in the prior 6 months, Number of ER visits in the prior 6 months, Charlson score, Total number of medications, Total number of BP medications, Dementia. Our AHS data team will be connecting with facilities approximately once per month to determine level of care designation (i.e LTC, LTC-D, SL, SL-D) on each new resident who is eligible to participate in BEDMED-Frail. The purpose of this data is to allow for adjustment of this variable, listed above.

**THE CASE FOR RANDOMIZATION WITH A WAIVER OF CONSENT:** As important as this work is, it is not feasible without a waiver of consent and it is important to clearly outline to the ethics board why we believe such a waiver is warranted.

1. The only change any patient will make in this trial is to a medication timing with evidence for greater safety (i.e. timing will not change for control institutions).
2. Patients and their families are not currently consulted about what time of day their medications are administered.
3. Current practice is to generally ignore the time of day patients took their blood pressure medication pre-admission and to administer those pills at an arbitrary time of the facilities choosing (typically morning for once daily medication).
4. Patients/families/primary care providers will be notified of the change in policy and given the opportunity to exempt their loved one / patient from participating.
5. After the initial change, patients and providers are free to change back to morning administration for any reason without the need for justification.
6. The vast majority of nursing home patients are unable to provide their own consent as a result of dementia, and family members are likely unable to provide that consent for them as a result of legislation.
7. If a waiver of consent is not possible the trial cannot go forward and the unique information to guide and optimize the care of such patients may never be obtained.

# *Log of BedMed-Frail Amendments*

| Date of Submission
(D-M-Y) | Date of Acceptance
(D-M-Y) | Summary of Amendment
(Wording as submitted to the ethics board)                                                                                                                                                                                                                                                                                                                                                                                                                                                                                                                                                                                                                                                                                                                                                                                                                                                                                                                                                                                                                                                                                                                                                                                                                                                                                                                                                                                                                                                                                                                                                                                                                                                                                                                                                                                                                                                                                                                                                                                                                                                                                                                                                                                                                                                                                                                                                                                                                                                                                                                                                                                                                                                                                                                                                                                                                                           |
|-------------------------------|-------------------------------|--------------------------------------------------------------------------------------------------------------------------------------------------------------------------------------------------------------------------------------------------------------------------------------------------------------------------------------------------------------------------------------------------------------------------------------------------------------------------------------------------------------------------------------------------------------------------------------------------------------------------------------------------------------------------------------------------------------------------------------------------------------------------------------------------------------------------------------------------------------------------------------------------------------------------------------------------------------------------------------------------------------------------------------------------------------------------------------------------------------------------------------------------------------------------------------------------------------------------------------------------------------------------------------------------------------------------------------------------------------------------------------------------------------------------------------------------------------------------------------------------------------------------------------------------------------------------------------------------------------------------------------------------------------------------------------------------------------------------------------------------------------------------------------------------------------------------------------------------------------------------------------------------------------------------------------------------------------------------------------------------------------------------------------------------------------------------------------------------------------------------------------------------------------------------------------------------------------------------------------------------------------------------------------------------------------------------------------------------------------------------------------------------------------------------------------------------------------------------------------------------------------------------------------------------------------------------------------------------------------------------------------------------------------------------------------------------------------------------------------------------------------------------------------------------------------------------------------------------------------------------------------------------------------|
| 05-11-2019                    | 08-11-2019                    | 
Our study has not yet started randomization. We wish to adjust our methods now to deal with an anticipated logistic issue related to how we will keep track of which patients are randomized to the intervention and which patients are randomized to control.
 
THE LOGISTIC ISSUE:
Our study was approved for cluster randomization, with each cluster being a ward or wing of a participating LTC facility (i.e. each facility would have multiple clusters within it). Our current process involves the data steward telling the facility which patients are eligible for the study, and subsequently learning from the facility which ward those patients are on so that the data steward can determine their allocation, record their allocation, and advise the pharmacist of whose medication timing needs to change. This requires dialog between multiple people (data steward, LTC administration, and pharmacist), is not easily automated, has more opportunity for error, and the process is ongoing over the course of the study because of patients being newly admitted (i.e. must take place many times).
 
THE SOLUTION:
It is much easier for the facility staff and data steward to carry out the study if we switch to patient level randomization / allocation performed by the data steward. In so doing, the data steward automatically and reliably knows the allocation of each patient and needs to send only a single easily automated communication to the pharmacist telling them which patients have been allocated to switch to bedtime BP medications. This would not materially change anything for the residents, who would still have a 50/50 chance of randomization and who would still have exactly the same opportunity to opt out. The data steward will still ask the facility to update the level of care of eligible residents periodically (for use as a covariate in analysis), but this can now be done less frequently and can be automated.
 
ADDITIONAL CHANGE:
We have also taken the opportunity of submitting this amendment to update our description of the flow of information between the facility, the research team, and the data steward needed to communicate:
 
1) Which patients have opted out of the study (and hence ensure those patients BP medication timing does not change).
 
 
• All residents and families will be notified of the trial and will have a minimum of 30 days to opt out of the trial by notifying caregivers, administrators, or the study team directly.
 
• Caregivers and administrators will notify the study team, and the study team will in turn notify the data steward, who will remove the resident from the study and ensure their name is not forwarded to the pharmacist for BP medication timing change.
 
 |

|            |            |                                                                                                                                                                                                                                                                                                                                                                                                                                                                                                                                                                                                                                                                                                                                                                                                                                                                                                                                                                                                                                           |
|------------|------------|-------------------------------------------------------------------------------------------------------------------------------------------------------------------------------------------------------------------------------------------------------------------------------------------------------------------------------------------------------------------------------------------------------------------------------------------------------------------------------------------------------------------------------------------------------------------------------------------------------------------------------------------------------------------------------------------------------------------------------------------------------------------------------------------------------------------------------------------------------------------------------------------------------------------------------------------------------------------------------------------------------------------------------------------|
|            |            | 
2) Which residents are currently residing in each facility prior to the initial randomization.
 
 
• The data steward will be requesting a list of all residents from each facility prior to the initial randomization so that they can verify they are accurately detecting all current residents prior to attempting to identify those who are eligible. The study team does not receive this information.
 
 
3) Identifying the level of care of eligible residents for use in baseline characteristics and as a covariate in analysis.
 
 
• To accomplish this, the data steward will periodically send via secure e-mail link a spreadsheet of eligible residents to an administrator designated by each facility. That administrator will then enter the level of care designation for each of their residents and return this to the data steward. Each facility designate will only see the names of their own residents.
 
 |
| 10-02-2020 | 11-02-2020 | In order to allow for AHS to utilize AHS datasets, we need to add them as a Research location under section 1.6 (Research Locations).                                                                                                                                                                                                                                                                                                                                                                                                                                                                                                                                                                                                                                                                                                                                                                                                                                                                                                     |
| 21-03-2022 | 22-03-2022 | Change in study coordinator contact information on documentation.                                                                                                                                                                                                                                                                                                                                                                                                                                                                                                                                                                                                                                                                                                                                                                                                                                                                                                                                                                         |
| 24-01-2023 | 30-01-2023 | A new process is being added: AHS and Alberta Health administrative data will be utilized between April 2002 and December 2025 for the purpose of determining patient characteristics and outcomes. Specifically, PIN will be used to determine Blood Pressure medication timing in the 30 days before randomization up to 6 months post randomization by using the medication instructions held within PIN using appropriate keyword searches.                                                                                                                                                                                                                                                                                                                                                                                                                                                                                                                                                                                           |
| 25-04-2023 | 25-04-2023 | 
1) We needed to change from [name]'s name to my name (new RC on project).
 
2) We noticed that the text speaks to the whole facility potentially changing timing, whereas participants are randomized at the patient level and only some individuals will have their timing changed. This likely happened because the original study protocol was for a cluster randomized trial. Hence we are asking to change a few words to show that individuals potentially have their timing changed, not the whole facility.
 
3) We also took the opportunity to change any reference to long term care, or supportive living, to "continuing care" which encompasses both levels of care. This will make it easier for some facilities, who have both supportive living and long term care sites, so that they only need to deal with a single version of the notification letter.
 
4) There was also a typo where an apostrophe was missing - and is now added.
                                                           |

|            |            |                                                                                                                                                                                                                                                                                                                                                                                                                                                                                                                                                                                                                                                                                                                                                                                                                                                                                                                                                                                                                                                                                                                                                                                                                                                                                                                                                                                                                                                                                                                                                                                                                                                                                                                                                                                                                                                                                                                                                                                                                                                                                                                                                                                                                                                                                                                                                                                                                                                             |
